#### D5. Measures

We will use multimethod, multiple indicator strategies to assess the constructs underlying the intervention theory.

*D5.1. Demographics:* The demographic interview was designed and tested in Georgia with samples composed of single mothers. Primary caregivers will report their yearly income, per capita income, employment status, duration of unemployment during the past 2 years, hours worked per week, education level, numbers of children and adults in the household, and relations of all household members to one another.

*D5.2. Autonomy-Promoting and Responsive Family Relationships:* Four characteristics of family relationships are hypothesized to prevent substance use: (1) emotional and instrumental support, (2) affectively positive relationships featuring open communication, (3) adaptive racial socialization, and (4) setting expectations for emerging adults and providing support for meeting them.

*D5.2a. Emotional and instrumental support:* Emerging adults and parents will complete the Family Support Inventory (FSI; Wills, Vaccaro, & McNamara, 1992), a 14-item measure of perceived availability of emotional and instrumental support from family members. Internal consistency ranged from .82 to .88 for emotional support and .76 to .83 for instrumental support with multiethnic samples of adolescents. The scales have good psychometric properties (Wills & Shinar, 2000) and consistently predicted less substance use, greater self-regulation, and more resilient coping in multiethnic samples of adolescents (Wills, Blechman, & McNamara, 1996; Wills, & Cleary, 1996; Wills, Windle & Cleary, 1998). In addition to the FSI, four items that Carver, Scheier, and Weintraub (1989) developed will be used to assess the frequency with which family members provide emotional support. These items were modified slightly in response to focus groups' feedback. The items' Cronbach's alphas in our prior prevention research ranged from .78 to .87 ([name] et al., in press); with multiethnic samples, they predicted more self-regulated coping and less adolescent substance use (Wills, Resko, Ainette, & Mendoza, in press).

*D5.2b. Affectively positive relationships featuring open communication:* Parents and emerging adults

will complete the Interaction Behavior Questionnaire (IBQ; Prinz, Foster, Kent, & O'Leary, 1979), which assesses affective involvement and positivity in family relationships. Cronbach's alphas for this scale with one of [name] and [name]'s longitudinal research samples ([name] et al., 2002) were .85 for adult caregivers and .79 for youths.

The Discussion Quality Scale ([name] et al., 1998) will be used to assess family discussions that involve emerging adults. Parents and emerging adults will be asked about the frequency and bi-directionality of their discussions regarding school, religion, and peers. Cronbach's alphas were .84 for mothers and .79 for youths. In the proposed study, four topics relevant to emerging adults and intervention-targeted behavior will be added: future work or education, substance use, management of racial discrimination in adult contexts, and plans for the future. Focus groups will evaluate these items prior to their addition to the assessment protocol.

Conflictual and ineffective communication will be assessed from parents' and emerging adults' perspectives using a modified version of the Ineffective Arguing Inventory (Kurdek, 1994). We adapted this instrument for our work with rural African American mothers and youths ([name] et al., 2002, 2004). The items' wording was revised based on focus groups' feedback and one item was dropped due to poor reliability. Internal consistencies for the resulting 7-item scale were .78 for parents and .70 for youths participating in [name] and [name]'s longitudinal research.

*D5.2c. Adaptive racial socialization:* Emerging adults and parents will complete Stevenson's (1997) Scale of Racial Socialization for Adolescents (SORS-A). The measure includes 4 subscales that assess various aspects of adaptive racial socialization. Cultural Pride Reinforcement indexes encouragement to take pride in African American culture; Racism Awareness Teaching involves helping emerging adults to be alert to racism and its consequences; Life Achievement Struggling emphasizes overcoming obstacles to achievement; and Extended Family Caring measures relatives' caregiving support. [name] and [name] reported good reliability and construct validity for this measure, which evinced sensitivity to prevention programming effects in SAAF ([name] et al., in press; [name] & [name], in press.) For the present study, we developed additional items that focus specifically on skills for managing racism in emerging adults' environments. Focus groups of rural African American parents will review the new items before the items are added to the assessment protocol.

*D5.2d. Setting expectations and responsibilities for emerging adults:* Emerging adults and parents will report the extent to which they discuss the future (Eccles & Barber, 1993), using items such as, "How much do you talk to your child about the job they would like to have when they're grown up?" and "My mom is helpful with plans for future education." McCabe and Barnett (2000) obtained Cronbach's alphas of .92 for youth reports and .90 for parent reports with a sample of African American families.

#### *D5.3. Additional Individual and Family Risk Factors:*

*D5.3a. Parenting congruence:* Parents will complete Ahrons' (1981) Quality of Coparenting Scales—Revised, which assess agreement on parenting issues. Cronbach's alpha from [name] and [name]'s research with a rural Georgia sample was .79 ([name] et al., 2002).

*D5.3b. Parental conflict:* Parents will complete the O'Leary-Porter Scale (Porter & O'Leary, 1980), indicating frequency of conflict with one another in the emerging adult's presence. Cronbach's alpha from our previous research with a rural Georgia sample was .79 ([name] et al., 2002).

*D5.3c. Parental depression:* The Center for Epidemiologic Studies Depression Scale (Radloff, 1977), which was designed for use with community samples, will be used to assess depression among parents. With rural Georgia samples, internal consistency averaged .84 and the scale was associated with competence-promoting parenting practices and co-caregiver conflict (see Section C).

*D5.3d. Parental substance use:* Parents and will respond to the Parent Alcohol/Drug Use History (Collins, Parks, & Marlatt, 1985). Items assess drinking in a typical week and both lifetime and recent use of marijuana, stimulants, sedatives, psychedelic drugs, cocaine, heroin, and opiates. Internal consistencies for caregivers in our prior prevention research ranged from .79 to .81.

*D5.3e. Emerging adults' psychological functioning.* Emerging adults' parents will complete the Child Behavior Checklist (Achenbach, 2000).

#### *D5.4. Community/Social Contextual Characteristics:*

*D5.4a. Discrimination:* Emerging adults and parents will report their experiences with racism using the Schedule of Racist Events (SRE; Landrine & Klonoff, 1996) and the Racist Hassles Questionnaire. We will use the Frequency Of Unfair Treatment Based On Race and Stress Of Racial Unfairness subscales of the SRE. Respondents rate the occurrence and stressfulness of racially based unfair treatment by school officials,

business employees, legal system officials, neighbors, church members, friends, and strangers. In [name] and [name]'s developmental research, Cronbach's alphas for youths and caregivers exceeded .75 for both subscales.

*D5.4b. Restricted educational and occupational opportunities:* The Total Resources subscale ( $\alpha = .95$ ) of the Community Problems and Resources Scale (CPRS; Forehand & [name], 2000), which we have used previously in our longitudinal studies, includes 19 positive community characteristics such as job training, educational facilities, social organizations, and transportation. For the proposed study, additional items were developed to target specific educational and job opportunities. Focus groups will evaluate these items before the items are added to the assessment.

*D5.4c. Financial stress:* Chronic financial difficulties will be assessed using scales that Conger and associates (e.g., Conger & Elder, 1994) developed as part of their work with rural families and subsequently used with the FACHS sample: Unmet Material Needs, Can't Make Ends Meet, Financial Adjustments, and Negative Financial Events. Reliabilities for the FACHS sample ranged from .69 to .80.

*D5.4d. Personal life stressors:* The number of negative life events that parents and emerging adults experienced in the past 12 months will be measured using a checklist that includes events such as criminal victimization, serious illness or injury, legal problems, and marital separation or divorce. This measure has been used in past longitudinal research on rural families (Conger & Elder, 1994). When used with African American adults in FACHS, it was significantly correlated with distress and severity of financial problems ( $ps < .001$ ).

#### *D5.6. Emerging Adults' Protective Intrapersonal Processes:*

*D5.6a. Self-control:* Emerging adults will complete the Self-Control Inventory (SCI; Wills & Stoolmiller, 2002), a 25-item instrument with subscales that measure good (soothability, dependability, planning, problem solving) and poor (impatience, distractibility, angerability) self-control. With adolescent samples, the scales' reliabilities ranged from .73 to .83, and the scores predicted substance use problems in both multiethnic (Wills et al., 2001, 2002) and African American (Wills, Gibbons, et al., 2000; Wills, Gibbons, et al., 2003) samples.

*D5.6b. Emotion regulation:* Emerging adults will report their coping styles using the Coping Responses Inventory (CRI; Moos, 1990, 1993). The CRI has been widely used with samples of adults who use substances; the eight subscales' internal consistencies range from .61 to .74 and are intercorrelated (average  $r = .29$ ; Moos, 1997). Emerging adults will also complete Wills and Hirky's (1996) coping processes inventory. The measure provides additional, situation-specific information on emerging adults' ways of dealing with typical problems at home and school. The proposed project will include the measure's anger-based coping and helpless coping subscales. In FACHS, the subscales' Cronbach's alphas ranged from .74 to .99 for caregivers and from .62 to .88 for youths (Gibbons & Simons, 2001).

*D5.6c. Future orientation:* Future orientation will be assessed using the future, present/hedonistic, and present/fatalistic subscales of the Time Perspective Inventory (Zimbardo & Boyd, 1997). The future subscale reflects planning goals and ways to achieve them ( $\alpha = .77$ ). The present/hedonistic subscale represents an orientation toward present enjoyment, pleasure, and excitement ( $\alpha = .79$ ). The present/fatalistic subscale indexes a belief that the future is predestined and cannot be influenced by individuals' actions ( $\alpha = .74$ ). Responses to an adapted version of this measure from an urban multiethnic sample were associated with self-regulation, anger-based coping, and self-esteem (Wills et al., 2001).

*D5.6d. Racial identity:* Racial identity will be assessed using the Centrality and Regard subscales of the Multidimensional Model of Racial Identity for African Americans (Sellers et al., 1997). [name] and [name] have used these scales successfully in their research ([name] et al., 2004). The Centrality subscale ( $\alpha = .70$ ) measures the extent to which being African American is central to the respondents' definitions of themselves. Regard ( $\alpha = .73$ ) refers to affective and evaluative perceptions of one's race.

*D5.7. Emerging Adults' Substance Use Prototypes and Behavioral Willingness:* A short version of Gibbons and Gerrard's (1995, 1997) risk prototype scale will be included. Participants will be given a brief explanation of the prototype concept (Gibbons & Gerrard, 1995; Gibbons, Gerrard, & Boney-McCoy, 1995), then be asked to "think for a minute about the type of person your age who (drinks alcohol; smokes pot)" and to indicate the extent to which the following terms describes that person: smart, popular, cool, dull (boring), good-looking, and childish. A parallel question assessing prototypes of non-users will be included (Gerrard et al., 1999). Participants also will indicate how similar they believe they are to each of these prototypes. Negative items will be reverse scored, so that high scores will reflect a favorable image. Cronbach's alphas in the

FACHS exceeded .70 for each scale.

Willingness to use substances will be assessed using items developed in our research with rural adolescents (Gerrard et al., 1999; Gibbons et al., 1998). Emerging adults will be asked to imagine a risk-conducive situation: "Suppose you were with some friends at a party and one of them offered you some kind of alcoholic drink." They will then be asked to indicate how likely they would be to do each of the following: leave the situation, tell them "no thanks," take it and try it, and have more than one drink. In prior studies with rural African American adolescents (Gibbons et al., in press), Cronbach's alpha for this scale was .86.

**D5.8. *Emerging Adults' Substance Use:*** The substance use assessment is designed to address the multidimensional nature of use (Newcomb, 1992). From three well-validated measures, items were selected for their sensitivity to intervention effects at several levels of substance use. At the initiation level, group differences in the proportion of participants who transition from nonuse to use during the study can be detected. At the escalation level, group differences in the proportion of participants who increase their frequency/intensity of use during the study can be assessed. At the problem use level, group differences in specific substance-related behaviors and problems can be indexed. The basic items in the measure are those included in the Monitoring the Future study (Johnston, Bachman, & O'Malley, 2002), which assess lifetime, annual, and 30-day prevalence and frequency of cigarette smoking, alcohol use, binge drinking, and marijuana use. For the purposes of the proposed study, a 6-month assessment will be added. A checklist of other drugs includes lifetime use of LSD/acid, Ecstasy, cocaine, heroin, other opiates, amphetamines, non-prescribed tranquilizers, and inhalants. Problems associated with substance use will be indexed using items from the Minnesota Student Survey for high school students (Harrison et al., 1998) assessing dependence (e.g., had to use more to get same effect, tried to cut down but couldn't) and negative consequences of use (e.g., use hurt relationships with friends or family, use interfered with other activities, use resulted in problems with law, missed school or work because of use).

#### **D6. *Plan of Analyses***

**D6.1. *Preliminary Analyses:*** Prior to executing psychometric analyses, distribution kurtosis and skew, means, and variances will be examined for each continuous variable, and appropriate transformations will be conducted on indicators with extreme kurtosis or skew. For limited dependent variables (dichotomous, count, or censored variables, see below), we will use statistical techniques appropriate for each variable, including logistic regression, Poisson, negative binomial, or Tobit regression, or proportional hazard models in the case of models for time-to-event outcomes, such as age at substance use initiation.

**D6.1a. *Reliability, construct development, and multi-informant analyses:*** For more than a decade, we have used multi-informant data from rural African Americans in our analyses. Building latent constructs from multi-informant data involves several steps. First, the construct is operationally defined, with items grouped into scales conceptually as well as through factor analysis and other multidimensional scaling techniques (Bentler, 1976). Items that meet internal consistency criteria (Cronbach's alpha) are then examined in a confirmatory factor analysis with SEM to demonstrate that the construct can be distinguished from other constructs and to establish convergent and discriminant validity. Because we will use many well-validated scales, we expect instrumentation issues to pose minimal analytic difficulties.

**D6.1b. *Attrition and missing data issues:*** For the proposed research, we will use two approaches to deal with incomplete data: Full Information Maximum Likelihood (FIML; Arbuckle, 1996; Marini, Olsen, & Rubin, 1980; McArdle, 1994; Muthén, Kaplan, & Hollis, 1987) and Multiple Imputation (MI; Heeringa & Rodgers, 1998; Rubin, 1987; Schafer, 1997). Both techniques correctly estimate population parameters and standard errors when data are "missing at random" Rubin (1987).

**D6.1c. *Intent-to-treat analyses:*** To preserve random assignment, the analyses will include all prevention families who complete the pretest, regardless of the number of prevention sessions they attend.

**D6.1d. *Baseline equivalence for prevention and control groups:*** Before testing the hypotheses, we will use hierarchical linear modeling (HLM; Bryk and Raudenbush, 1992) to conduct statistical comparisons between prevention and control group members on all study variables. Because participants will be recruited from schools, we will use HLM to examine pretest differences among youths attending different schools. School-level effects will be included in tests of the hypotheses if they account for unique variance at baseline.

**D6.2. *Substance Use Outcome Measures:*** The assessment of substance use (see Section D5.8) covers initiation, escalation, and problem use. SAAF—EAP intervention effects will be examined for use, frequency of use, and quantity used during the past 30 days, 6 months, and 1 year. We can determine lifetime use for all

substances from the history-of-use questions, identifying movement from nonuse to initiation of use for specific substances. We will use discrete event-history models to examine SAAF-EAP effects on initiation over the 3 repeated measures.

**D6.3. *Power Analysis:*** As mentioned in Section D1, 690 families will be recruited to allow for an attrition rate of 15%. Power analyses were based on an effect size of .30 (Durlak & Wells, in press). Table 9.4.1 in Cohen (1977) can be used to calculate a necessary sample size of around 150 families per group to detect differences between the prevention and comparison groups with an alpha of .01 and a power of .90 for the dependent measures. For the analyses presented below using structural equation modeling (SEM), we considered both sample size and statistical power issues. The literature on sample size for latent variable structural equation analysis suggests that 150 cases are enough to ensure a reliable estimation of the model (see discussion by Tanaka, 1987). Much of this literature, however, is based on Monte Carlo studies of factor analysis models involving relatively few parameters (e.g., Boomsma, 1982). An alternate perspective is to consider the available sample size relative to the number of parameters that the model is estimating. For example, Bentler (1985) recommends at least 5 cases per parameter. We expect to have a sufficiently large sample to permit testing of the causal models described below. Based on the parameters derived from the research described in Section C, we conducted power analyses using Jöreskog and Sörbom's (1993) LISPOWER program. Our analyses evaluated the model's ability to detect the statistical significance of path coefficients that vary in their "true" magnitude, holding the other parameters in the model constant at values derived from the analyses presented in Section C. These power calculations were significantly different from 0 at  $p < .05$ . We evaluated the statistical power of these models for samples that varied in size from 150 to 170 cases. For the causal paths included in the models discussed in Section C, the power was above .80 for detecting path coefficients of .17 to .20 in absolute magnitude for samples of 150 cases or more. These coefficients correspond to those that Cohen (1988) termed small effects. These results suggest that we will have sufficient power to detect even relatively weak relations among variables.

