Several important issues must be considered that, due to space limitations, cannot be addressed in detail. First, research on LGM with substance use suggests that an S-shaped logistic function may be more appropriate than a linear function (see McArdle, 2002; Spoth, Redmond, Shin, & Azevedo, 2004). Second, as in any intervention study, the missing data mechanism must be integrated into the analytic plan while considering patterns commonly observed in a mixture model. For example, the groups may include participants engaging in low levels of substance use at the beginning of the study who do not increase their use, early initiators who maintain their initial use levels, participants who increase use gradually, and so forth. We will address this issue by integrating the missing data mechanism (e.g., Hedeker & Gibbons, 1997) and the various types of trajectories (e.g., Muthén, 1997; Nagin & Tremblay, 2001) into a single integrated analytic framework. In addition to this approach, we will also estimate random effects Tobit models using Stata. This allows for the censoring of substance use at 0. Nonusers may vary in the strength of their avoidance of usage; some may be seriously considering trying a particular substance whereas others have no intention whatsoever of using. We will evaluate these models in comparison with others appropriate for our outcome measures, including zero-inflated Poisson and negative binomial models (Long, 2003).

*D6.4b. Aim 5: Testing mediational paths in the causative model:* With our proposed sample size and design, we should be able to detect an effect size of .20 or greater 80% of the time with an alpha of .05 (Muthén & Curran, 1997). The sample is larger than needed for detection of significant group differences because we also plan to contribute to theory development by testing mediational pathways; proposing a framework for exploratory analyses; examining moderators of change; comparing various developmental trajectories; and identifying all relevant individual, intervention-related, and time-varying covariates in our analyses.

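### AIM's initiation test pre-specifies no pretest predictor, although own-substance use is constant among those who can still start and other candidate predictors are already collected

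*Combined protocol and SAP*

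**What the plan says.** All references are to the AIM part of the combined document.

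- **The test.** D6.2: "We will use discrete event-history models to examine SAAF-EAP effects on initiation over the 3 repeated measures". No covariate is listed. The same section derives the event from lifetime-use questions, "identifying movement from nonuse to initiation of use for specific substances". D5.8 describes the initiation outcome as "the proportion of participants who transition from nonuse to use during the study".
- **Adjustment rules.** The one rule tied to the hypothesis tests is in D6.1d: "School-level effects will be included in tests of the hypotheses if they account for unique variance at baseline". D6.4b, on mediation, gives "identifying all relevant individual, intervention-related, and time-varying covariates in our analyses" as one reason for the size of the sample. It names no variable and no selection rule.
- **Candidate predictors.** D5.8 covers "lifetime, annual, and 30-day prevalence and frequency of cigarette smoking, alcohol use, binge drinking, and marijuana use", plus a checklist of other drugs. D5.7 adds: "Willingness to use substances will be assessed using items developed in our research with rural adolescents". A pretest is planned for everyone (D2, D4).
- **Differences among nonusers.** D6.4a says of nonusers that "some may be seriously considering trying a particular substance whereas others have no intention whatsoever of using". It uses this to motivate a random-effects Tobit model, not the initiation model.

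**The concern.** A baseline measure of the outcome is usually the first covariate to consider in a randomised comparison. Here it is unavailable: everyone who can still start a substance has the same pretest value for it. Any prognostic information must come from other pretest variables, and the initiation model names none.

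In a logistic hazard model, omitting a baseline variable that predicts the event lowers the power of the test of the programme effect. The at-risk group is a subset of the sample, and the plan gives no power for this test. A free gain is therefore worth taking, and covariates named before follow-up data are seen leave no later choice to defend.

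**Working it through.** **1. The plan's own figure.** The documents state no power or sample size for initiation. The nearest figure is D6.3's roughly 150 families per group, for an effect size of .30, alpha .01 and power .90. Read as a two-sided comparison of standardised means, n = 2(z₀.₉₉₅ + z₀.₉₀)²/d² = 2 × 14.88/0.09 ≈ 331 per group, so it does not reproduce on that reading. That is a separate matter, and nothing below depends on it.

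**2. Who is at risk.** D6.1c and D6.2 state no risk set for initiation. The definitions in D5.8 and D6.2 imply one: a move from lifetime nonuse to use can be made only by someone who had never used that substance at pretest. Three assessments give 3 − 1 = 2 intervals in which it can happen. Within this set, pretest lifetime use has no variance and cannot act as a covariate.

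**3. Size of the power loss.** From the documents: 370 families, equal allocation (Specific Aims) and 15% attrition (D6.3), so 370 × 0.85/2 ≈ 157 per arm. Everything else is assumed: 30%, 50% or 70% never-users (47, 79 or 110 per arm), two-sided alpha .05, and a two-interval discrete-time logit model with one continuous pretest risk score.

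*Simulation A*: cumulative initiation 40% control against 25% prevention, 3,000 trials per setting, Monte Carlo SE about .009. Power without → with the score:

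| Never-users per arm | OR 2.0 per SD | OR 2.5 per SD |
|---|---|---|
| 47 | .357 → .394 | .331 → .403 |
| 79 | .532 → .587 | .520 → .609 |
| 110 | .649 → .711 | .664 → .746 |

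The gain is .013 to .021 at an odds ratio of 1.5 per SD, and .075 to .127 at 3.0.

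*Simulation B*: control initiation 30% or 50%, marginal odds ratio 0.5 (prevention 17.6% or 33.3%), 94, 157 or 220 never-users in total, 2,000 trials per setting.

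| Log-odds per SD | Gain over the six settings |
|---|---|
| 0 | none beyond simulation error (for example .426 → .426) |
| 0.5 | .018 to .036 |
| 1.0 | .055 to .117 |
| 1.5 | .129 to .212 |

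With no programme effect (157 never-users, 30% initiation), the rejection rate was .042 without and .044 with an uninformative score, and .050 and .048 with a score of log-odds 1.0.

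**4. Sensitivity to the sample-size conflict.** Specific Aims and D1 give 370 families; D6.3 gives 690 and attaches the 15% attrition to that number. With 690, 690 × 0.85/2 ≈ 293 per arm, or 88, 147 and 205 never-users. Use power ≈ Φ(h√(n/2) − 1.96), with h = 2arcsin√.40 − 2arcsin√.25 = 1.369 − 1.047 = 0.322:

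| Never-user share | Unadjusted power, 370 families | Unadjusted power, 690 families |
|---|---|---|
| 30% | .34 | .57 |
| 50% | .53 | .79 |
| 70% | .67 | .90 |

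The 370 column agrees with simulation A. The starting power therefore depends heavily on which total is correct.

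**The case against.** The strongest reply is that D6.2 is one sentence naming a class of model. It lists no terms at all, not even interval terms, so silence is not exclusion, and D6.4b shows that the investigators expect to use covariates. This stands: the defect is lack of pre-specification. But the D6.4b phrase names no variable, and the intervention-related and time-varying covariates it includes may themselves be affected by assignment, so it does not supply a baseline adjustment for this test.

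Four stronger readings are tempting and are not supported:

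- *That initiation has the smallest sample in Aim 1.* Aim 1 also concerns existing users, and no never-user share is given. At 70% never-users there would be 110 per arm against 157 − 110 = 47 existing users.
- *That covariates will be chosen from the outcome data.* D6.4b describes no such procedure; it leaves the choice open.
- *That the unadjusted test is invalid.* It is a randomised comparison, and the simulated rejection rate with no programme effect was .04 to .05 either way.
- *That willingness is a ready covariate for every substance.* The only willingness scenario described in D5.7 is an offer of an alcoholic drink. Nothing shows that it predicts starting cigarettes or other drugs.

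It is also fair to say that the risk set is inferred (D6.1 separately allows proportional hazards models for age at initiation), that predictor strength is assumed, and that the simulations used one continuous score where the remedy is mainly a yes/no variable. These points limit how far the gain can be quantified; they do not reverse its direction for a covariate that truly predicts starting.

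**Conclusion.** The point holds as an inexpensive improvement in efficiency. The initiation test is specified with the programme effect only; own-substance use cannot serve as the baseline covariate among those at risk; and usable alternatives are collected and left unassigned.

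Under the assumptions above, the power forgone is about 1 to 13 percentage points for odds ratios of 1.5 to 3.0 per SD. It reaches about 21 points for a very strong predictor (log-odds 1.5 per SD) and is nil for an uninformative one. These are illustrations of scale: the never-user share, initiation rate and predictor strength are not in the documents, and the total sample is stated in two ways. Neither the absolute power nor any single gain should be quoted as a property of this trial.

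**What to change.** Amend D6.2 to state that:

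- each initiation model is fitted in participants who had never used that substance at pretest, with a separate intercept for each of the two intervals;
- any pretest use of another listed substance (yes/no) is a fixed covariate, and the pretest willingness score is added where its items concern that substance;
- a standardised risk difference is reported beside the adjusted odds ratio;
- covariates for this test are not chosen from follow-up data by arm. If a fallback for sparse events is wanted, fix in advance a threshold on the total number of initiators pooled over arms, below which only other-substance use is kept.

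The cost is a few sentences and no new data. The adjusted odds ratio is conditional on the covariates, which is why the standardised risk difference should accompany it, and the gain will be small if the covariates predict weakly. The 370 and 690 totals should be reconciled before any power for this test is quoted.
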